## Abstract

**Background:**

There is increasing interest in carrying out pre-induction cervical ripening on an outpatient basis. However, there are concerns about the use of prostaglandins, the agents commonly used in hospital settings for this indication, because prostaglandins induce uterine contractions that may lead to fetal hypoxia. Indeed, in a recent study we demonstrated abnormalities in 9% of fetal heart rate tracings performed following prostaglandin induced cervical ripening at term. In contrast, we confirmed in the same study that isosorbide mononitrate (IMN) (administered on an inpatient basis) was both effective in inducing cervical ripening at term, and was associated with no associated fetal heart rate abnormalities.

**Methods/design:**

The aim of this study is to determine whether IMN self administered by women on an outpatient basis improves the process of induction of labour. Specifically, we hypothesise that the use of outpatient IMN will result in a shorter inpatient stay before delivery, decreased costs to the health service and greater maternal satisfaction with ripening and induction of labour, compared with placebo treatment.

In the study described here (the "IMOP" study), women scheduled for induction of labour at term, and who require pre-induction cervical ripening will be randomised to self-administer at home either IMN 40 mg, or a placebo, each vaginally, at 48 hours, 32 hours and 16 hours before scheduled hospital admission.

After admission to hospital, treatment will revert to the usual induction of labour protocol. We will compare the primary outcomes of the elapsed time interval from hospital admission to vaginal delivery, the costs to the health service of induction of labour, and women's experience of induction of labour in the two groups.

**Discussion:**

This trial will provide evidence on the efficacy of outpatient IMN for pre-induction cervical ripening at term. We will study a formulation of IMN which is cheap and widely available. If the treatment is effective, acceptable to women, and cost effective, it could be implemented into obstetric practice worldwide.

**Trial registration:**

The trial has been registered on the International Standard Randomised Controlled Trial Number Register (ISRCTN) and given the registration number ISRTN39772441.

## Background

### Outpatient cervical ripening

Around 20% of pregnant women undergo induction of labour in the UK [1]. In primigravidae, the mean time taken from induction to delivery is between 15 and 20 hours, of which up to 12 hours is spent in the cervical ripening phase before labour itself starts. There is increasing interest in carrying out cervical ripening on an outpatient basis. Outpatient cervical ripening with prostaglandins is associated with significantly shorter admission to delivery times [2,3] and/or reduced health care costs [4]. Perhaps the most significant factor in favour of outpatient cervical ripening is women's endorsement: women were much more likely to report high satisfaction rates with outpatient compared with inpatient cervical ripening (56% v 39%, p < 0.008) [5]. However, there are concerns about the use of prostaglandins, the agents commonly used in hospital settings for this indication, and their use for outpatient cervical ripening has been declared unsafe by many authorities because of the potential for uterine contractions to cause fetal hypoxia which would remain undiagnosed in the outpatient environment [6,7]. In a recent study we demonstrated abnormalities in 9% of fetal heart rate tracings performed following prostaglandin induced cervical ripening at term. In contrast, we confirmed in the same study that IMN (administered on an inpatient basis) was both effective in inducing cervical ripening at term, with no associated fetal heart rate abnormalities.

### Properties of the ideal cervical ripening agent

An agent that ripened the cervix without stimulating uterine activity would be the ideal cervical ripening agent for outpatient use. We have previously demonstrated that vaginal IMN administered on an inpatient basis is an effective cervical ripening agent in the first trimester [8,9]. We have also shown that vaginal IMN, in the doses and at the gestation planned here, has no clinically significant adverse effects on either maternal or fetal haemodynamics [10]. In our recently published "PRIM" study [11] we found that IMN 40 mg was an effective cervical ripening agent at term. These findings are supported by the recent work of Ekerhovd et al, who showed that cervical resistance was reduced by 50% 4 hours after treatment with 40 mg vaginal IMN at term [12]. In contrast to prostaglandins, nitric oxide donors inhibit rather than stimulate uterine contractions, and promote rather than restrict uterine blood flow. Thus nitric oxide donors such as IMN appear to be the ideal cervical ripening agent for outpatient use.

### Why is a trial needed now?

To our knowledge, there are no systematic reviews on outpatient induction of labour. A Medline search using the headings "outpatient" and "cervical ripening" and restricted to studies in the English language on human subjects generated 22 publications, of which 17 are relevant to this application [2-4,6,7,13-26]. A search of the Cochrane Controlled Trials Register using the same key words did not reveal any additional studies. The majority of published studies on outpatient cervical ripening have used prostaglandins as the active agent. One has examined the use of Dilapan [26] and one a transcervical Foley catheter [24].

We found no systematic reviews or studies investigating the use of IMN for outpatient cervical ripening. Two studies have reported on the clinical use of nitric oxide donors for cervical ripening at term on an inpatient basis. In the first, 500 μg of the nitric oxide donor glyceryl trinitrate was associated with fewer episodes of uterine tachysystole compared with 3 mg PGE_2 _[27]. In the second 40 mg IMN (up to three doses at 6 hour intervals) was associated with fewer adverse events overall (including tachysystole) compared with 50 μg of the prostaglandin misoprostol (up to three doses at 6 hours intervals) [28]. In both of these studies, whilst the nitric oxide donor was considered effective, it was less effective than the comparator prostaglandin on an inpatient basis.

There is increasing interest in outpatient cervical ripening. This interest is driven at least in part by financial costs associated with an inpatient stay in the labour ward. The estimated cost for 24 hour labour ward stay is £500 – £1000 [North Glasgow University Hospitals Trust Finance department – personal communication], thus a 30% reduction in the inpatient ripening phase of 12 hours would be associated with a cost saving of £75 – £150 per patient. Additionally, there is a wish to "deinstitutionalise" the process of labour, and, where appropriate, to offer women the opportunity to remain as an outpatient for a longer period of time. Hofmeyer notes that information on women's views on cervical ripening and induction of labour are conspicuously lacking [29]. A small number of studies, including Biem et al (2003) [5] and PRIM [11] have provided some pilot evidence that women report positive views about outpatient cervical ripening. Additionally, self administration of vaginal tablets on an outpatient basis is acceptable to women in other clinical situations [30]. There is as yet no research evidence on the views of women who have experienced IMN induced cervical ripening in an outpatient setting, and women's acceptance of the novel situation of "pre-induction cervical ripening induction at home" is vital to its ultimate success. IMOP will address not only the clinical efficacy of outpatient administration of IMN for pre-induction cervical ripening, but also the economics of this strategy together with an assessment of women's views and experiences.

We believe that IMN may be the most appropriate pre-induction cervical ripening agent for outpatient use, since its uterine relaxant properties (in contrast to the uterine stimulant effects of prostaglandins) obviate the main reason for continuous fetal heart rate monitoring. A trial of outpatient IMN is particularly timely, because we have recently demonstrated the efficacy, safety and patient acceptability of inpatient cervical ripening with IMN in the PRIM study. In the PRIM study cervical ripening with IMN (two doses of 40 mg 16 hours apart) was compared on an inpatient basis with the agent conventionally used in the Princess Royal Maternity, Glasgow (prostaglandin gel, two doses of 2 mg, 16 hours apart). Briefly, the use of IMN as a cervical ripening agent was significantly more acceptable to women than the prostaglandin used as an alternative (mean [SD] visual analogue score of maternal satisfaction with treatment of 7.03 [2.71] with IMN compared with 5.79 [3.07] with prostaglandin, p < 0.0001). We also confirmed that inpatient treatment with IMN was not associated with events that would preclude outpatient use. The PRIM study evaluated the inpatient use of IMN for cervical ripening. However, we believe that it is as outpatient therapy where the effects of IMN may be the most significant advance in cervical ripening. The "IMOP" study described here will be the first to evaluate the use of IMN in this setting. We consider that it is particularly timely to embark on such a trial now, given that data from the PRIM study suggests that outpatient use of IMN is likely to be safe and effective.

## Methods and trial design

### Aims of the trial

The aim of this trial is to test the hypothesis that IMN, 40 mg every 16 hours to a total of three doses improves the process of induction of labour. Specifically we aim to test the hypotheses that outpatient pre-induction cervical ripening with IMN:

i. Reduces the elapsed time from hospital admission to delivery

ii. Reduces the costs of induction of labour

iii. Improves women's experience of induction of labour

iv. Does not increase operative delivery rates

Women scheduled for induction of labour at term, and who require pre-induction cervical ripening will be invited to participate in the study. Participants will be randomised into an active (IMN) or a control (placebo) group and asked to self-administer either IMN 40 mg, or a placebo, each vaginally, at 48 hours, 32 hours and 16 hours before scheduled admission. After admission to hospital, treatment will revert to the usual induction of labour protocol whereby prostaglandins are given until cervical ripening is achieved, and fetal membrane rupture is performed thereafter, followed by syntocinon if contractions do not start spontaneously. Data on the outcome measures listed below will be collected and compared in the two groups.

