### Trial design

IMOP is a double blind, randomised, placebo controlled trial in a single clinical setting. Active and placebo treatment will be allocated in a 1:1 ratio. The primary outcome measures are the effect of outpatient pre-induction cervical ripening with IMN on:

i. The elapsed time from hospital admission to delivery (defined as the time from admission to inpatient induction or admission in labour to delivery – either vaginally or by caeserean section)

ii. The costs of induction of labour

iii. Women's experience of induction of labour (maternal satisfaction)

iv. Operative delivery rates

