#### Secondary

iv. Primary clinical outcome (elapsed time from admission to delivery) for the subgroup of women who deliver vaginally

v. Operative delivery rates

vi. Incidence of unscheduled admission for reasons other than labour commencing

vii. Duration and frequency of neonatal admissions to special care

viii. Incidence of adverse maternal and fetal outcomes such as uterine hypercontractility, postpartum haemorrhage (maternal outcomes) and meconium stained liquor, five minute Apgar of less than seven (fetal outcomes)

ix. Length of labour

x. Oxytocin augmentation rates

xi. Epidural usage

xii. Proportion with unfavourable cervix at 24 hours after admission

xiii. Requirement for additional inpatient cervical ripening agent

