## Statistical analysis ground rules

The primary endpoint of time from admission to delivery will be compared between the two groups using a two sample two sided t-test, and then adjusted for covariates that are pre-specified as important using a linear model. The analysis will be performed at the conclusion of the study. Analysis of secondary outcomes will be using t-tests (or Wilcoxon tests) or chi-squared tests as appropriate to the distribution of the data, again with adjustment for covariates using appropriate generalised linear models.

All statistical analyses will be fully specified in a Statistical Analysis Plan, which will be signed off before the treatment codes are broken. All primary analyses will be according to the intention to treat principle. No interim analyses will be performed, other than those requested by the Data Monitoring committee. The results of these interim analyses, and/or any other unblinded data will not be revealed to the investigators or the Trial Steering Committee until after the study is complete.

Analysis of the questionnaire data will be carried out using SPSS and analysis of variance. Interviews and focus groups will be coded and analysed using a computer package (ATLAS Ti) used to facilitate analysis of qualitative data for emergence of salient themes.

A prospective economic evaluation will be conducted alongside the randomised controlled trial to estimate the cost-effectiveness of outpatient cervical ripening with IMN prior to induction of labour. The cost differences between the two groups, the IMN and placebo groups, will be measured, valued and combined with the clinical effectiveness data from the trial. The economic evaluation will incorporate data from all subjects recruited into the trial. The valuation of all resource inputs will be consistent with the notion of opportunity cost.

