The economic evaluation will be conducted from a health service perspective and will take two forms; (i) an overall cost analysis and (ii) an incremental cost-effectiveness analysis, which will be expressed in several forms, for example, incremental cost per operative delivery prevented [34]. All analyses will be conducted on the basis of intention to treat. Outcomes and costs for the experimental and control groups will be compared using relative risks and 95% confidence intervals for dichotomous variables, Mann-Whitney-U tests for ordinal variables, and Student's t-tests for interval variables where parametric assumptions are met. Fieller's theorem will be used to calculate 95% confidence intervals for incremental cost-effectiveness ratios [35]. In the absence of stochastic data for all variables, a series of multi-way sensitivity analyses will be undertaken to explore the implications of uncertainty on the base-case incremental cost-effectiveness ratios. In addition, cost-effectiveness acceptability curves will be constructed using the net benefits approach [36]. All analyses will be performed with a microcomputer using Statistical Package for the Social Sciences (SPSS) software, version 11.5.

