## Discussion

We believe that outpatient IMN will reduce the time from hospital admission to delivery, reduce the costs of induction of labour and improve women's experience of induction of labour (with no increase in operative delivery rates). This trial will determine whether these hypotheses are correct. If so, we anticipate that women undergoing induction of labour in the UK and in other countries worldwide could use outpatient IMN as soon as the finding are published, since the formulation of IMN we plan to investigate in this study is cheap and widely available.

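### Aim iv claims that IMN does not increase operative delivery, but the tests named are tests of difference and the sample size was not set for this outcome, so a non-significant result cannot establish it

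*Protocol article*

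**What the plan says.** Aims of the trial introduces four aims with "Specifically we aim to test the hypotheses that outpatient pre-induction cervical ripening with IMN"; the fourth is "Does not increase operative delivery rates". The Discussion repeats it: "with no increase in operative delivery rates). This trial will determine whether these hypotheses are correct".

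Operative delivery appears under "The primary outcome measures are the effect of outpatient pre-induction cervical ripening with IMN on" in Trial design, but the Outcomes section lists "Operative delivery rates" as a secondary outcome. That conflict is a separate matter; the present point holds under either status.

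Statistical analysis ground rules gives the tests: "Analysis of secondary outcomes will be using t-tests (or Wilcoxon tests) or chi-squared tests as appropriate to the distribution of the data". The same sentence adds covariate adjustment by generalised linear models. The economic evaluation at the end of that section says that outcomes and costs will be "compared using relative risks and 95% confidence intervals for dichotomous variables", and gives the cost per operative delivery prevented as an example of a cost-effectiveness ratio.

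The sample size calculation covers time from admission to delivery and, separately, maternal satisfaction. It gives no expected rate and no power for operative delivery. The article states no limit of acceptable increase anywhere.

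**The concern.** Aims i to iii claim an improvement, and a significant difference in the right direction supports such a claim. Aim iv claims the absence of harm. A test of difference takes no difference as its null hypothesis, and failing to reject that null leaves open any increase that the data cannot exclude. Unless operative delivery falls significantly, the tests named can never give a positive answer to aim iv. They can only fail to contradict it.

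At stake is what the trial may conclude on operative delivery. The Discussion makes no increase one of the hypotheses that must prove correct before it anticipates use of outpatient IMN. If that part rested on a non-significant test in a trial not sized for the outcome, low power could pass for reassurance.

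**Working it through.** **Inputs from the protocol article.** 150 women per arm, two-sided 5% level, difference of 4 hours and SD of 9 hours (Sample size calculation).

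**Assumptions.** Control operative delivery rates p of 20–60%, because the article gives none. Increases of 5, 10 and 15 points are for illustration only.

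**1. The plan's own figure.** Standard error = 9 × √(2/150) = 1.039 hours. 4/1.039 = 3.849, and 3.849 − 1.96 = 1.889, so power is 97.1% (97.0% by the noncentral t distribution) against the 96% stated. The stated power for satisfaction also reproduces (93.4% against 93%). The sample size is sound for the outcomes it was set for.

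**2. Precision for operative delivery if the true rates are equal.** With SE = √(2p(1−p)/150):
- the 95% half-width for the risk difference is 1.96 × SE;
- the smallest increase that can be excluded with 80% power (one-sided 2.5%) is (1.96 + 0.84) × SE = 2.80 × SE.

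**3. Power of the difference test for a true rise d.** Let p̄ be the mean of the two rates. Power = Φ{[d − 1.96√(2p̄(1−p̄)/150)] / √[(p₁(1−p₁) + p₂(1−p₂))/150]}. For p₁ = 0.40 and p₂ = 0.50: (0.10 − 1.96 × 0.0574)/0.0572 = −0.22, so power is 41%.

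| Control rate | 95% half-width (points) | Excludable with 80% power (points) | Power, +5 | Power, +10 | Power, +15 |
|---|---|---|---|---|---|
| 20% | 9.0 | 12.9 | 18% | 52% | 83% |
| 30% | 10.4 | 14.8 | 15% | 44% | 77% |
| 40% | 11.1 | 15.8 | 14% | 41% | 74% |
| 50% | 11.3 | 16.2 | 14% | 41% | 75% |
| 60% | 11.1 | 15.8 | 14% | 44% | 80% |

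**4. An example.** Suppose 60/150 (40%) deliver operatively on placebo and 75/150 (50%) on IMN.
- Chi-squared without continuity correction: z = 0.10/0.0574 = 1.74, p = 0.08, not significant.
- Risk difference: SE = √((0.24 + 0.25)/150) = 0.0572, giving 10 points with a 95% interval of −1 to +21.
- Relative risk: 0.50/0.40 = 1.25, SE of its logarithm √(1/60 − 1/150 + 1/75 − 1/150) = 0.129, 95% interval 0.97 to 1.61.

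The test does not reject, yet the interval includes a rise of 20 points. The relative risk interval shows this as plainly as the risk difference, but with no limit fixed beforehand neither says whether aim iv is met.

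**The case against.** **More than a bare chi-squared test is planned.** This is correct. The generalised linear models can give adjusted effect estimates, and the economic evaluation plans relative risks with 95% intervals and names operative delivery. The interval needed is therefore largely in the plan already. What is lacking is any link between that interval and acceptance of aim iv.

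**A reader might infer that the plan means to take a non-significant result as proof of no harm.** No section says so. What the documents support is narrower: a hypothesis that the trial promises to settle, and named tests that cannot settle it.

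**The analysis plan or the fuller protocol may set a margin.** Either may, and the absence of one from an article is not in itself a fault. But the hypothesis, the type of test and the sample size are all stated here and do not fit together. A margin set elsewhere would not change what 300 women can exclude.

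**Adoption does not hang on this outcome.** This stands in part. The Abstract makes implementation depend on efficacy, acceptability and cost-effectiveness, without naming operative delivery. In the Discussion it is a parenthesis, though the condition that follows does include it.

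**The figures rest on an assumed rate.** They do. At a 20% control rate, power for a 10-point rise is 52%, so it cannot be said in general that such a rise would be missed more often than not. The conclusion does not turn on which rate applies.

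**The outcome is secondary, and the trial is powered on another.** This bears on the weight of the point but does not remove it.

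**Conclusion.** The point holds as a mismatch between aim iv and the means given to answer it. A non-significant difference in operative delivery cannot establish that IMN does not increase it. With 150 per arm and assumed control rates of 20–60%, power to detect a true 10-point rise is about 41–52%, the 95% half-width is about 9–11 points, and the smallest increase that can be excluded with 80% power under equal true rates is about 13–16 points. All of these use normal approximations and full data on 300 women.

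This is a recommended change of wording and analysis, not a defect that undermines the trial. The analysis of time to delivery, its sample size and the data collection are unaffected.

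**What to change.** - Reword aim iv and the matching sentence of the Discussion as estimation: the difference in operative delivery between the arms, as a risk difference or relative risk with a two-sided 95% confidence interval.
- State in Statistical analysis ground rules that a non-significant test will not be taken as evidence of no increase.
- State the limited precision: about 9–11 points either side of the estimate under the assumed rates, to be recalculated from the unit's own operative delivery rate.
- If the no-increase claim is kept, accept it only when the upper confidence limit lies below a margin that the sponsor fixes and justifies before unblinding. Say at the same time what 300 women can exclude. The choice of margin is a clinical judgement for the sponsor.

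**Cost.** Wording in the protocol and analysis plan, with no new data and no change to the sample size. The downside is a more modest safety claim: the trial would report how large an increase it can exclude, not that there is none.
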